A Cochrane review [8] examined the effects of tDCS in individuals with Parkinson’s disease. Meta-analyses, based on two trials, suggested that tDCS improves motor skills, measured by the Unified Parkinson’s Disease Rating Scale (UPDRS)—part III—(MD − 14%; 95% CI − 25 to − 4), but has no effect on walking speed (SMD 0.5; 95% CI − 0.2 to 1.2) compared with sham intervention. More recently, a systematic review [12] reported that tDCS provides no clinically important benefits over walking training on walking speed, step length, or cadence in people with Parkinson’s disease. Given that most trials included individuals with mild impairments or did not investigate effects on mobility and falls, the purpose of this randomized trial is to examine the effects of the addition of tDCS to walking training on walking, mobility, and falls in individuals with moderate walking limitations due to Parkinson’s disease. The specific research questions are as follows:
In people with Parkinson’s disease, is walking training associated with tDCS superior to walking training alone for improving walking (speed, step length, cadence, confidence), mobility, and falls?Are any benefits maintained beyond the intervention period?

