### Randomization

Randomization will be computer-generated, by a researcher not involved in participant recruitment, and stratified according to the baseline walking speeds: slow (≤ 0.5 m/s) and intermediate (0.51 to 1.0 m/s) walkers, to ensure an even spread between the groups (1:1 allocation). The allocation of the participants will be concealed in sequentially numbered and sealed in opaque envelopes, prepared prior to the study by a research assistant, who will not be involved in the study. After the baseline measures have been collected, participants will be randomly assigned to the experimental or control group by the treating therapist, after revealing the content of the sealed opaque envelopes. All outcomes will be measured by blinded assessors. All enrolled participants will receive a code, in order to protect confidentiality before, during, and after the trial.

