### Sample size estimation

Twenty-four participants will be recruited, with walking speed as the primary outcome. The sample size has been calculated, to reliably detect a between-group difference of 0.18 m/s in walking speed, with 80% power, at a two-tailed significance level of 0.05. In previous trials [9, 16, 25] with similar samples of community-dwelling people with Parkinson’s disease who received tDCS associated with walking training, the mean walking speed of the participants was 0.73 m/s (SD 0.15 m/s), measured by a timed-walking measure. The least number of participants needed to detect a 0.18 m/s difference between two independent groups, which would indicate a change in the UPDRS walking category [26], is 11 per group, i.e., 22 participants in total. Based on the assumption that about 10% of participants may drop out during the study, a target of 24 participants in total has been set.

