### Statistical analyses

Data collection will yield eight variables: walking speed (m/s), walking step length (m), walking cadence (steps/min), walking confidence (modified Gait Efficacy Scale score; 10–100), mobility (TUG; seconds), freezing of gait (New Freezing of Gait Questionnaire; 0–28), fear of falling (FES-I Brazil score; 16–64), and number of falls. There are two factors (group × time), with repeated measures on the time factor. Two-way analyses of variance with repeated measures at all time points for all outcomes will be reported to evaluate the statistical significance of the between-group differences. The mean between-group differences, along with 95% confidence intervals, will be reported for all outcomes. The effect of the intervention will be calculated based on intention-to-treat analyses.

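### The ANOVA named as the significance test leaves open which term or week decides the primary outcome, and its group term is not the single 0.18 m/s comparison the trial was sized for

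*Protocol article*

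**What the plan says.** All of this is in the protocol article.

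- **Sample size estimation.** The trial is sized "to reliably detect a between-group difference of 0.18 m/s in walking speed". Power and error rate are set by the phrase "with 80% power, at a two-tailed significance level of 0.05". The comparison is a "difference between two independent groups", with SD 0.15 m/s and 11 per group before dropout. No visit is attached to the 0.18 m/s.
- **Statistical analyses.** On how the arms will be compared: "Two-way analyses of variance with repeated measures at all time points for all outcomes will be reported to evaluate the statistical significance". The factors are group and time, repeated on time. Mean between-group differences with 95% confidence intervals are also promised, without a visit or a way of handling baseline.
- **Design.** Outcomes are taken at weeks 0, 4 and 8, so the ANOVA over all time points has the baseline visit as one of its three outcome levels. Under Randomization, allocation follows the baseline measures.
- **Primary outcome.** Comfortable walking speed, with no primary time point.
- **Background, research questions.** Superiority is asked first. A separate second question is "Are any benefits maintained beyond the intervention period".

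**The concern.** The sample size rests on one contrast, while the stated significance test is a model with several terms. The article does not say which of them settles the primary outcome. Two terms could be read as testing the between-group differences, and they test different things:

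- The group main effect is the arm difference averaged over three visits. At one of these the true difference is zero by randomisation.
- The group-by-time interaction is a 2-df test that the arm difference varies over visits. It does not say at which visit the arms differ.

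The same data could therefore give opposite answers depending on the term chosen. If the choice is made after unblinding, neither the stated power nor the 5% error rate is secured. The group term also does not estimate the 0.18 m/s that the article justifies as a shift in UPDRS walking category.

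**Working it through.** **Inputs from the article:** difference 0.18 m/s; SD σ = 0.15 m/s at a visit; two-sided 5%; 80% power; 1:1 allocation; n = 11 per arm; visits at weeks 0, 4 and 8. **Assumed, because the article does not give it:** correlation r between visits of 0.5 to 0.9, equal for every pair of visits, with the same SD at each visit.

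**1. The plan's own figure.** n = 2(1.960 + 0.842)² × 0.15²/0.18² = 10.90, rounded up to 11 per arm. This reproduces the stated number as a single two-sample comparison at one visit. The normal approximation gives 80.4% power at n = 11, and the exact t calculation gives 76.3%. The powers below are on the t or F basis, so 76% is the like-for-like benchmark.

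**2. What the group term tests.** With expected differences (0, d4, d8), it tests (0 + d4 + d8)/3:
- sustained: (0 + 0.18 + 0.18)/3 = 0.12 m/s
- halved by week 8: (0 + 0.18 + 0.09)/3 = 0.09 m/s
- week 4 only: (0 + 0.18 + 0)/3 = 0.06 m/s

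**3. Power of the group term.** The SD of a participant's three-visit mean is σ√((1 + 2r)/3): 0.122 at r = 0.5, 0.134 at 0.7 and 0.145 at 0.9. The standard error is that SD × √(2/11), with noncentral t on 20 df.

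**4. Power of the interaction.** λ = (n/2) Σ(d_t − d̄)² / (σ²(1 − r)), with noncentral F on 2 and 40 df. The sum of squares is 0.0216 for the sustained and week-4-only patterns and 0.0162 for the halved pattern. At r = 0.5, λ = 5.5 × 0.0216/0.01125 = 10.56, or 7.92 if halved.

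**5. Power of a baseline-adjusted week-4 contrast.** The residual SD is σ√(1 − r²): 0.130, 0.107 and 0.065. The difference is 0.18 m/s in every pattern, with noncentral t on 19 df.

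| Test, 11 per arm | Pattern | r = 0.5 | r = 0.7 | r = 0.9 |
|---|---|---|---|---|
| Group term | sustained | 59% | 51% | 46% |
| Group term | halved by week 8 | 38% | 32% | 28% |
| Group term | week 4 only | 19% | 17% | 15% |
| Interaction | sustained or week 4 only | 81% | 96% | >99% |
| Interaction | halved by week 8 | 68% | 89% | >99% |
| Week 4, baseline-adjusted | any of the three | 87% | 96% | >99% |

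The formula in step 5 ignores chance baseline imbalance; a simulation at r = 0.7 gave about 95%. With all 24 participants retained (12 per arm), the group term reaches only 63–49%, 41–31% and 21–16%. For 80% power it would need 18–24, 31–42 or 67–93 per arm.

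**6. Type I error if either ANOVA term could count.** Under equal correlation the two tests are independent, so 1 − 0.95² = 9.75%. Simulation with 40,000 runs gave 9.6% to 9.8% for r from 0.5 to 0.9.

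**The case against.** Four points can be made on the other side.

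- **The interaction is the usual treatment test in a pre/post randomised design, and it is well powered.** This stands in large part. A reader might infer from the group-term figures that the trial is underpowered. The documents do not support that: the interaction falls below 80% only for the halved pattern at the lower correlations. But the article does not name the interaction, its wording about between-group differences fits the group term equally well, and a 2-df test does not identify week 4.
- **The inflated error rate presupposes a rule that the article does not state.** This also stands. A reader might infer that the plan runs at about 10%, or at about 14% if change-score tests at weeks 4 and 8 also counted. No passage lets whichever test is significant decide, and the mean differences are presented as estimates with intervals, not tied to particular weeks. The 10% describes what an open choice between the two terms would permit. It is not a property of a stated rule.
- **Week 8 is not a rival primary endpoint.** Correct. A reader might take weeks 4 and 8 as co-primary because all time points enter the test, but nothing gives week 8 that status, and the order of the research questions suggests week 4 comes first.
- **The deciding term is normal content for an analysis plan that is not shown, and two-group sizing is common for repeated-measures trials.** Silence alone would be no finding, and the simple formula is not wrong in itself. Here, however, the article does state the significance test, and one natural reading of it conflicts with the sizing in the section just before.

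**Conclusion.** The point holds in a limited form. The stated test does not fix the term or week that decides the primary outcome. One of its two plausible readings, the group main effect, tests a difference of 0.12 m/s or less in the three patterns examined, at 15% to 59% power, where the article claims 80% for 0.18 m/s. The other reading, the interaction, has 68% to over 99% power but does not answer at which visit the arms differ.

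The dilution from 0.18 to 0.12, 0.09 or 0.06 m/s needs only randomisation and the assumed course of the effect. The power figures also rest on the article's SD of 0.15 m/s at every visit and on an assumed equal correlation of 0.5 to 0.9; the group term stays below 60% with 11 per arm across that range. A general shortage of power and an established inflation of the error rate are not shown.

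**What to change.** Name one primary test in Statistical analyses, for example:

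> The primary analysis is the between-group difference in comfortable walking speed at week 4, adjusted for baseline speed (ANCOVA, or a mixed model with week 0 as a covariate and not as an outcome level), two-sided 5%. The baseline-adjusted difference at week 8 is secondary and addresses maintenance. Omnibus ANOVA terms, if reported, are descriptive.

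Attach week 4 to the 0.18 m/s in Sample size estimation and to the definition under Primary outcome, so that the three sections agree. The change uses data already collected, follows the order of the research questions, and needs no extra participants under the article's own difference and SD. The cost is wording only, but the choice must be recorded before any unblinded analysis.

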## Methods

### Design

A prospective, randomized controlled trial with concealed allocation, blinded assessors, participants and therapists, and intention-to-treat analysis will be carried out (Fig. 1). Community-dwelling people with Parkinson’s disease will be recruited from the general community, by means of advertisements and by screening public rehabilitation services and lists of previous observational or cross-sectional research projects. Participants will be randomly allocated into either experimental group (i.e., walking training with tDCS) or control group (i.e., walking training with sham-tDCS). Outcome measures will be collected by trained researchers at baseline (week 0), at the end of the intervention (week 4), and 1 month beyond the intervention (week 8). Measurements and interventions will be conducted during the on phase of medication. Analyses of the inclusion criteria, getting the informed consent, data collection, and statistical analyses will be carried out by researchers, who will be blind to the group allocation. All the participants will be evaluated and receive all the information regarding the interventions in a research laboratory. The study obtained ethical approval from the Institutional Research Ethical Committee (CAAE 06952819.6.0000.5060) of the Universidade Federal do Espírito Santo, Vitória, Brazil. The trial was prospectively registered at the Ensaiosclinicos.gov.br, Registry: RBR-6bvnx6 (www.ensaiosclinicos.gov.br/rg/RBR-6bvnx6/).

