## Discussion

This trial will examine the efficacy of the addition of tDCS to walking training for improving walking, mobility, and falls in people with Parkinson’s disease. Although previous studies [9, 10, 15, 16, 27] have investigated the combined effect of tDCS and walking training, methodological shortcomings (e.g., design and very small sample sizes), characteristics of interventions (e.g., duration of intervention, type of exercises), and characteristics of the participants (e.g., level of disabilities) prevent drawing clear conclusions, which could help clinicians in their decision-making process. In addition, many trials did not investigate whether benefits carry over to improving mobility and falls. In response to this challenge, a triple-blinded randomized trial will be conducted. High internal validity is expected, due to randomization, concealed allocation, blinding of assessors, participants and therapists, intention-to-treat analysis [28], and appropriate sample size.

Previous studies suggest that tDCS modulates cortical excitability during stimulation by non-synaptic changes of the cells, and increasing evidence indicates that the aftereffects of tDCS are driven by synaptic modification [29]. Synaptic plasticity could, therefore, induce long-lasting excitability changes in the central nervous system. Although the neurophysiological effects of tDCS have been identified and its safety has been proved [29, 30], the clinical effects remain unclear. This trial focuses on identifying the effects of the addition of tDCS on walking parameters commonly affected in individuals with Parkinson’s disease [3, 31]. If neurophysiological benefits of tDCS are carried over to clinical benefits, clinicians will assure an important tool to help reduce disabilities related to the continuous death of dopamine-producing cells in the *substantia nigra*. Less expensive portable devices are currently available, making direct current potentially ideal as an adjunct to other physical interventions [30].

This trial has some limitations. The experimental and control interventions consist of walking exercises delivered three times per week over 4 weeks and, therefore, depend on participants’ motivation, adherence, and commitment. Strategies to encourage participants to comply with the protocol, such as contracts and phone calls, are planned.

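### The named repeated-measures ANOVA does not deliver the promised intention-to-treat analysis unless missing visits are imputed, and the article states no imputation

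*Protocol article*

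**What the plan says.** Three statements in the protocol article bear on this point.

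- **Method.** Statistical analyses describes the design as "There are two factors (group × time), with repeated measures on the time factor" and names the test: "Two-way analyses of variance with repeated measures at all time points for all outcomes will be reported". The Design section sets three assessments, at weeks 0, 4 and 8.
- **Principle.** The same section says "The effect of the intervention will be calculated based on intention-to-treat analyses". The Abstract and the Design section repeat the promise. The Discussion relies on it, listing "blinding of assessors, participants and therapists, intention-to-treat analysis [28], and appropriate sample size" among the reasons to expect high internal validity.
- **Expected losses.** Sample size estimation puts the requirement at 11 per group (22 in total), assumes that "about 10% of participants may drop out during the study", and concludes that "a target of 24 participants in total has been set".

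The article gives no imputation rule, mixed model or other means of keeping a participant with a missing visit in the ANOVA.

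**The concern.** As conventionally run, a two-way repeated-measures ANOVA works on a complete participant-by-visit table. A participant missing one of the three visits is removed from the whole analysis, not only from the visit that was missed. Someone measured at weeks 0 and 4 but absent at week 8 would then contribute nothing to the end-of-intervention comparison, although the primary-outcome value had been collected.

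Two things are at stake. The trial could report intention-to-treat while leaving out randomised participants. And if those who leave differ between arms, the comparison is no longer the one that randomisation protects. In arms of about 12, each person carries real weight.

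**Working it through.** **Inputs.** From Sample size estimation: target difference 0.18 m/s, SD 0.15 m/s, two-sided alpha 0.05, power 80%, 11 per group, 24 recruited, dropout about 10%. From Design: three visits. Not in the document: the timing of dropout, the arm in which it falls, its relation to outcome, and the correlation between visits.

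**Step 1. Reproduce the plan's figure.** n per group = 2 × (1.96 + 0.84)² × (0.15/0.18)² = 10.9, rounded up to 11, so 22 in total. This matches. Allowing for dropout, 22/0.90 = 24.4, against the stated 24, a matter of rounding that I do not pursue.

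**Step 2. Participants analysed under the named method.** With 10% lost, 24 × 0.90 = 21.6 are complete, so about 21 to 22 are analysed and 2 to 3 excluded.

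**Step 3. How likely is the conflict to arise?** If each participant is lost independently with probability 0.10, the chance that all 24 are complete is 0.9²⁴ = 0.08. At least one exclusion then has probability 0.92. If instead 10% missed each of the two follow-up visits independently (an assumption, not the plan's), complete cases would number 24 × 0.9² = 19.4.

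**Step 4. Power.** The 22 completers are the number the plan says it needs. At 11 per group, power for a simple two-group comparison is 80.4% by the normal approximation and 76.3% by the t distribution. Losing about two people is therefore already counted in the plan.

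**Step 5. Can the bias be sized?** Only by assuming who leaves. The expected minimum of 12 standard normal values is −1.63. The scenarios below take 12 per arm, and the change scores assume a correlation of 0.7.

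| Assumed loss | Contrast | Shift in the difference |
|---|---|---|
| Slowest at week 4, active arm only | Raw week-4 means | 1.63 × 0.15/11 = 0.022 m/s (12% of 0.18) |
| Slowest at week 4, active arm only | Change from baseline | 0.022 × (1 − 0.7) = 0.007 m/s (4%) |
| Least improved, active arm only | Change from baseline | 1.63 × 0.15 × √0.6/11 = 0.017 m/s |
| Slowest at week 4, one from each arm | Raw week-4 means | about 0 |

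The standard errors of the difference at 12 per arm are 0.15 × √(2/12) = 0.061 m/s for raw means and 0.15 × √0.6 × √(2/12) = 0.047 m/s for change. Every shift is well below one standard error. The spread, from nothing to 12% of the target, comes entirely from assumptions that the document does not supply.

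**The case against.** The strongest reply is that the article never mentions completers or listwise deletion. An ANOVA run on imputed data would satisfy both the method and the principle, and a condensed article may leave missing-data handling to a fuller plan that is not shown. This stands as a condition: the conflict exists unless missing visits are imputed. It does not remove the point. The objection is not that a detail is absent, but that the named test, applied literally under the article's own dropout assumption, defeats a property the article claims as a strength. A fuller plan that simply carries this wording over inherits the problem.

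A reader might infer that the result would be biased towards tDCS by about 0.022 m/s, on the ground that people doing poorly tend to leave. The document does not support this. It says nothing about who leaves or from which arm, and that figure is a one-arm extreme on the raw week-4 contrast. On the change contrast, which is closer to the planned group-by-time analysis, it falls to about 0.007 m/s. It vanishes if the slowest participant is lost from each arm.

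The timing of loss is also unknown. Week-4 data are discarded only for those who attend week 4 and miss week 8. Someone who leaves before week 4 has no follow-up speed to discard. Nor does a mixed model cure everything: it assumes data are missing at random, so bias remains if loss depends on values never observed.

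Finally, a reader might infer that participants who stop training would no longer be measured. The article does not say so, and its intention-to-treat commitment points the other way.

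**Conclusion.** The point holds in conditional form. As written, and without imputation, the planned ANOVA would analyse about 21 to 22 of 24 randomised participants under an intention-to-treat label. On the plan's own 10% figure, with independent losses, at least one exclusion is very likely (about 92%).

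This rests on the conventional form of the ANOVA being used, no imputation being specified elsewhere, and dropout near the assumed rate. It does not rest on any particular direction or size of bias, neither of which can be determined from the document. The sample size is not undermined. What is affected is the intention-to-treat claim and the use of data already collected. It should be corrected, but it does not invalidate the trial.

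**What to change.** For the continuous outcomes, replace the ANOVA with a likelihood-based linear mixed model with group, time and group × time. Include every randomised participant in the allocated arm with all available visits, and use small-sample degrees of freedom (Kenward-Roger, for example). Report the week-4 and week-8 between-group contrasts with 95% confidence intervals, which also meets the article's promise of mean differences with intervals.

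An acceptable alternative is to keep the ANOVA and pre-state a multiple imputation of missing visits.

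Because the mixed model assumes data missing at random, add one simple sensitivity analysis for informative dropout. For example, shift the imputed values for missing visits by a range of amounts, separately by arm, and report whether the conclusion changes. State in the report how many participants in each arm contribute at each visit.

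The cost is analysis wording and standard software. No new data, visits or participants are needed, and the change should be fixed before unblinding.
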